# Remote Monitoring Telemedicine (REMOTE) Platform for Patients With Anxiety Symptoms and Alcohol Use Disorder: Protocol for a Case-Control Study

**DOI:** 10.2196/16964

**Published:** 2020-06-24

**Keywords:** digital health, digital biomarkers, digital phenotype, mental health

## Abstract

**Background:**

Monitoring mental health outcomes has traditionally been based on heuristic decisions, often based on scarce, subjective evidence, making the clinical decisions made by professionals, as well as the monitoring of these diseases, subject to flaws. However, the *digital phenotype*, which refers to the analysis of data collected by measuring human behavior with mobile sensors and smart bracelets, is a promising tool for filling this gap in current clinical practice.

**Objective:**

The objectives of this study are to develop the digital phenotyping of patients with alcohol use disorder and anxiety symptoms using data collected from a mobile device (ie, smartphone) and a wearable sensor (ie, Fitbit) and to analyze usability and patient satisfaction with the data collection service provided by the app.

**Methods:**

We propose to conduct a study among a group of 60 participants split into two subgroups—experimental and control—of 30 participants each. The experimental group will be recruited by physicians from the Hospital Clínic de Barcelona, and the control group will be recruited on a volunteer basis through fliers and social media. All participants will go through pretraining to ensure technological capability and understanding of tasks, then each participant will download the HumanITcare app and will be given a wearable sensor (ie, Fitbit). Throughout the 4-month period, participants will be monitored on a range of factors, including sleep cycle, heart rate, movement patterns, and sociability. All data from the wearable sensors and the mobile devices will be saved and sent to the HumanITcare server. Participants will be asked to complete weekly questionnaires about anxiety, depression, and alcohol use disorder symptoms. Research assistants will ensure timely responses. The data from both sensors will then be compared to the questionnaire responses to determine how accurately the devices can predict the same symptoms.

**Results:**

The recruitment phase was completed in November 2019 and all the data were collected by the end of December 2019. Data are being processed; this process is expected to be completed by October 2020.

**Conclusions:**

This study was created and conducted as a pilot study with the Hospital Clínic de Barcelona, with the purpose of exploring the feasibility of our approach. The study is focused on patients diagnosed with anxiety and alcohol use disorder, but participants were also monitored for depressive symptoms throughout the trial, although these were not part of the initial inclusion criteria. A limitation to our study was the exclusive use of Android smartphones over iOS devices; this could result in a potential selection bias, due to the accessibility and affordability of Android phones as opposed to iOS-based phones. Another limitation might be that reviews of usability and satisfaction could be confounded by factors such as age and familiarity. An additional function that we might add in future studies is the ability for patients to manage their own data.

**International Registered Report Identifier (IRRID):**

DERR1-10.2196/16964

## Introduction

### Background

In the European Union (EU), approximately 165 million people suffer from mental health disorders, namely anxiety, mood disorders, and substance abuse. These mental health disorders have resulted in both direct and indirect global economic costs estimated at US $2.5 trillion in 2010, with the indirect costs (US $1.7 trillion) being significantly higher than the direct costs (US $0.8 trillion), contrasting the trends of other key diseases, such as cardiovascular disease and cancer [1]. Concurrently, problematic alcohol consumption is considered the causal factor of more than 200 diseases, leading to 5.1% of all global diseases and damages being attributed to alcohol abuse. In addition to the health risks this poses, the social and economic damages involved not only for individuals suffering from alcohol abuse but for society in general must be taken into consideration [2].

Monitoring mental health outcomes has traditionally been based on heuristic decisions, often based on scarce, subjective evidence, making the clinical decisions made by professionals, as well as the monitoring of these diseases, subject to flaws [3]. However, the *digital phenotype*, which refers to the analysis of data collected by measuring human behavior with mobile sensors and smart bracelets, is a promising tool for filling this gap in current clinical practice, offering objective evidence in an otherwise subjective field of diagnosis, namely through the utilization of digital biomarkers [4].

Biomarkers are physiological, pathologic, or anatomic characteristics measured objectively and used to evaluate a patient’s health in the status quo by comparing their current biomarkers to ideal, healthy biomarkers. In the wake of advancing technology, *digital biomarkers* are emerging as a new form of tracking patients’ health. Digital biomarkers are considered digital as they utilize sensors and computational tools to collect data. These measurements can be taken outside of a traditional clinical environment using sensors such as mobile devices and wearable sensors [5].

Numerous studies have shown that information collected from behavioral and physiological sensors can be used to improve conventional evaluations of patients with symptoms of anxiety. In addition, patients who use these platforms show higher levels of consistency with their treatment plans than those involved only in conventional practice [6]. There are various examples of the effectiveness of digital phenotype data collection in analyzing anxiety disorders:

There exist significant patterns between the time spent in certain places and presence of depression and anxiety, although these relationships were not consistent [7].It has been shown that sensors integrated into smart bracelets measuring conductance and skin temperature can be utilized to reach 78.3% (148/189) accuracy in classifying students into groups of high or low stress levels. Furthermore, the sensors provided a 79% (37/47) accuracy rate for classifying students’ states of mental health [8].Furthermore, analysis from sensors tracking GPS location and incoming and outgoing text messages and calls collected from 54 college students over a 2-week period indicated that levels of social anxiety can be predicted with an accuracy of up to 85% by tracking these variables [9].

Alongside digital tracking of anxiety symptoms, there also exist various apps designed to facilitate the monitoring of alcohol consumption in patients with alcohol use disorder [10-12]. Although more research is needed, these apps have been shown to be effective in increasing patients’ abilities to manage their conditions [10], leading to reduced days of consumption risk [11]. In addition, these tools allow for patients’ usual professional caretakers to monitor their conditions, allowing for more informed care [10]. Therefore, with the REMOTE (Remote Monitoring Telemedicine) Study, we aim to provide valuable insights and knowledge about digital biomarkers in alcohol use disorders and anxiety disorders.

### Study Objectives

Due to emerging research on digital biomarkers and the accuracy of passive monitoring of data in patients with mental health disorders, we propose to conduct the REMOTE Study among a group of 60 participants split into two subgroups of 30 participants each This study will be conducted in the Addictions Unit at the Hospital Clínic de Barcelona. The primary objective of this study is to analyze the digital physiological patterns of two groups of participants—one group with symptoms of anxiety disorder and alcohol use disorder and one healthy control group without these disorders—using data collected from a mobile device (ie, smartphone) and a wearable sensor (ie, Fitbit). The data will be collected from the sensors through the HumanITcare platform. The data will then be compared with the symptoms validated in clinical questionnaires, which participants will complete four times over the course of the study, in order to determine whether the use of sensor data is an efficient and accurate means of presenting objective diagnoses rather than the subjective diagnoses of the status quo.

The secondary objective of this study is to analyze usability and patient satisfaction with the data collection service provided by the app and to explore the feasibility of this approach in clinical practice.

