## Methods

### Design

#### Overview

This study is a case-controlled, prospective study consisting of two groups: one group of healthy control individuals who do not have symptoms of alcohol use disorders or anxiety and one experimental group that meets the selection criteria described in the Study Population and Setting section. Participants in both groups will be matched for age and sex, since both can be confounding factors regarding usage patterns of electronic devices. Both groups will receive mobile and wearable sensors that will track their physiological and behavioral activity over the course of 1 month. Both groups will also take the State-Trait Anxiety Inventory (STAI) [13], the Beck Depression Inventory-II (BDI-II) [14], and the Alcohol Use Disorders Identification Test (AUDIT) [15] once per week through the HumanITcare app downloaded on their phones. Participants will be instructed on the use of the app during the initial visit, along with receiving their wearable sensors (ie, Fitbits). The data will be monitored by the research team through an online, encrypted compilation of participants’ data.

The HumanITcare platform allows for the collection of data from the participants; the platform also provides a source of data for the researchers to verify that each participant’s data are being collected appropriately and that the Fitbit devices are working properly. The HumanITcare app that participants download to their phones collects data from the phones and sends them to the HumanITcare platform. As stated above, the app sends notifications to the participants once a week to remind them to complete the questionnaires. Also, it provides a *help* button so they can contact the researchers if needed (see the HumanITcare App section below).

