#### Study Population and Setting

The study will be conducted at the Hospital Clínic de Barcelona and is a single-center national study. Experimental participants will be drawn from the outpatient clinic at the Addictions Unit of the Hospital Clínic de Barcelona, and control group participants will be drawn from random volunteers recruited through fliers and social media.

The research team members at the Hospital Clínic de Barcelona Addictions Unit will be tasked with finding eligible subjects for the experimental group. The inclusion criteria for the experimental group participants are as follows: must be between the ages of 18 and 70 years; must have knowledge and daily use of new technologies; must have an alcohol use disorder, based on the Diagnostic and Statistical Manual of Mental Disorders, 5th Edition (DSM-5) [16]; must have significant anxiety symptoms (STAI score >33rd percentile); and must have been informed about the study and signed the data processing consent form. Potential experimental group participants are not eligible if they meet any of the following criteria: their mobile device is not compatible with the Android mobile operating system (OS); they have a diagnosis of affective disorder, based on the DSM-5; they have cognitive deficits that prevent proper participation; or they actively consume other substances, in addition to alcohol, except nicotine.

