#### Recruitment

There will be a total of 60 participants split between the experimental and control subgroups (see Figure 1).The recruitment of the 30 experimental patients, conducted by psychiatrists and clinical psychologists, will take place in the outpatient clinic and day hospital of the Addictions Unit of the Hospital Clínic de Barcelona. The usual health care professionals for patients with anxiety symptoms will refer the selected patients to the research team who will assess whether the selected patients meet the eligibility criteria. The 30 healthy control participants will be recruited using brochures distributed by the Faculty of Medicine at the University of Barcelona, as well as through social media.

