### Outcomes

#### Primary Outcome: Sensor Data Accuracy and Efficiency

The symptoms of anxiety and alcohol use disorder presented to the research team will be derived from the algorithm calculated from data collected by the HumanITcare platform (ie, app) and the Fitbit devices. These symptoms will be compared with the diagnoses provided by the status quo, *gold standard* questionnaires—the STAI [13] and the DSM-5 [16]—to determine the feasibility and efficiency of using objective sensor data in place of the current subjective methods of diagnosing mental health disorders. This will be done in a two-step process: first, by determining the relationship between the individual types of data tracked by sensors (eg, distance traveled and sleep schedule) and levels of anxiety and alcohol use disorder symptoms as presented by the questionnaires; and second, by using a mathematical model to estimate questionnaire scores by solely using the data collected by sensors (see Table 1). The primary outcome will be the efficiency of the developed algorithm’s ability to predict disorder symptoms.

**Table 1 table1:** Data collection by sensors compared with questionnaires.

Type of data being collected		Method of data collection

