#### Statistical Methods

The statistical analysis will be carried out as described in this section. Data collected from Fitbit devices, smartphones, and surveys from both groups will be interpreted with descriptive statistics. For the entire group, including all experimental and control participants, the mean and median will be calculated to determine the central tendencies. Next, we will find the standard deviation and range of the data to determine the variability within the dataset. The same process will be done for each group—experimental and control—individually, for the purpose of between-group comparison. The data will also be split and compared based on the source of the data: device information versus survey information.

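### The case-control contrast identifies only the combined condition and cannot support separate alcohol and anxiety biomarkers; for the graded STAI and AUDIT scores the confounding is strong but partial

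*Protocol article*

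**What the plan says.** The Protocol article defines two groups, which Study Objectives describes as "one group with symptoms of anxiety disorder and alcohol use disorder and one healthy control group without these disorders". For cases, Study Population and Setting makes two conditions compulsory together: each participant "must have an alcohol use disorder, based on the Diagnostic and Statistical Manual of Mental Disorders, 5th Edition (DSM-5") and "must have significant anxiety symptoms (STAI score >33rd percentile"). The comparison group is "one group of healthy control individuals who do not have symptoms of alcohol use disorders or anxiety" (Methods, Overview). Recruitment allows no third group: "There will be a total of 60 participants split between the experimental and control subgroups", 30 in each. Matching is on age and sex.

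The aims are partly joint and partly disorder by disorder. The abstract and Study Objectives describe patients who have both conditions. The Background, however, closes with "we aim to provide valuable insights and knowledge about digital biomarkers in alcohol use disorders and anxiety disorders". The first step of the primary outcome relates each type of sensor data to "levels of anxiety and alcohol use disorder symptoms as presented by the questionnaires", and the second estimates the questionnaire scores from sensors alone.

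On analysis, Statistical Methods says "For the entire group, including all experimental and control participants, the mean and median will be calculated", followed by measures of spread and the same summaries in each group so that the groups can be compared. The Discussion names depressive symptoms, phone type with socioeconomic status, and age and familiarity as sources of confounding or bias. It does not mention the overlap of anxiety and alcohol.

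**The concern.** When both conditions are present in every case and absent in every control, a sensor feature that differs between the groups may reflect drinking, anxiety, their combination, or something else about being an addiction-unit patient. The contrast gives no means of choosing between these.

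The graded scores inherit part of the problem. Selection makes STAI and AUDIT rise together across the pooled sample even if they are unrelated among patients. A feature driven by alcohol alone will then tend to correlate with STAI as well, and the reverse holds for one driven by anxiety. A model that estimates STAI from sensors can also look accurate in the pooled sample by telling patients from volunteers, without tracking anxiety among patients. The results are meant to inform a larger study, so a feature credited to the wrong disorder would be carried forward.

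**Working it through.** The article gives 60 participants without an effect size, SD, alpha or power, so it has no figure to reproduce here. The check has four steps.

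**1. Group status.** Code 30 cases as (anxiety 1, alcohol 1) and 30 controls as (0, 0). The design matrix [intercept, anxiety, alcohol] has rank 2 rather than 3, and the two indicators correlate at exactly 1. This needs no assumption and does not depend on sample size. It also applies wherever the DSM-5 alcohol diagnosis is the yardstick, since that diagnosis coincides with group.

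**2. Graded scores.** Let the groups differ by d1 within-group SDs on STAI and d2 on AUDIT, with within-group correlation ρ. With equal groups, the pooled correlation is

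r = (ρ + d1·d2/4) / √[(1 + d1²/4)(1 + d2²/4)].

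- ρ = 0, d1 = 0.5, d2 = 2: 0.25 / √(1.0625 × 2) = 0.17.
- ρ = 0.2, d1 = 1, d2 = 2: 0.70 / √(1.25 × 2) = 0.44.
- ρ = 0.2, d1 = 1.5, d2 = 3: 1.325 / √(1.5625 × 3.25) = 0.59.

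The overlap is substantial but below 1, so the scores are not fully aliased.

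**3. False attribution.** I simulated 20,000 studies per setting with 30 + 30 participants and one value per participant. The sensor depends on alcohol only, either through the AUDIT score (within-group r = 0.4) or as a 1 SD shift with disorder status. The separations, ρ and sensor effects are assumptions; the article gives none of them. The table shows how often the pooled sensor-STAI correlation is significant at two-sided 5%:

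| STAI / AUDIT separation (SD) | Sensor follows AUDIT, ρ = 0 | Sensor follows AUDIT, ρ = 0.2 | Sensor follows status (either ρ) |
|---|---|---|---|
| 0.5 / 2 | 11% | 24% | 13% |
| 0.5 / 3 | 16% | 31% | 13% |
| 1 / 2 | 24% | 44% | 34% |
| 1 / 3 | 44% | 65% | 34% |
| 1.5 / 2 | 42% | 61% | 57% |
| 1.5 / 3 | 70% | 85% | 57% |

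The same data under other analyses:

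- Within cases, unadjusted: 5-7%.
- Within cases, adjusted for AUDIT: about 5% throughout.
- Pooled, adjusted for AUDIT only: about 5% if the sensor follows the score, but 5-22% if it follows status.
- Pooled, adjusted for AUDIT and group: about 5% throughout.

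The table is not an upper bound. The article states no STAI cut-off for controls. If they lay at or below the 33rd percentile of a normal reference population, the STAI separation would be about 2.7 SD. A run with separations of 2.75 and 3 SD and ρ = 0 gave 99.5% (sensor r = 0.5 with AUDIT) and 84.5% (1 SD shift with status).

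**4. Precision within cases.** The Discussion reports one dropout from the experimental group, leaving 29 cases. At two-sided 5% and 80% power (assumed), the detectable correlation is tanh[(1.96 + 0.84)/√26] = 0.50. It is 0.49 with 30 cases. Partialling out AUDIT at n = 29 gives tanh(2.80/√25) = 0.51. The 95% half-width around zero is tanh(1.96/√26) = 0.37.

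**The case against.** Much of the article targets the combined condition, and the comparison with healthy controls estimates that properly. The Background sentence is a general aim that could be read jointly. The primary outcome is predictive, and predicting a STAI score does not require a sensor to be specific to anxiety. The scores are graded and planned four times per participant, and the case threshold on STAI leaves room for spread among cases. A condensed article may leave within-case models and mutual adjustment to a fuller plan. The study is a feasibility pilot whose data are already collected.

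Most of this stands and limits the point. The combined phenotype and score prediction are legitimate targets, and I do not count the unstated adjustment as an omission. What remains is that the design is fixed here, and no later plan can make the group contrast separate two conditions that always occur together. The first step of the primary outcome also names anxiety and alcohol symptom levels separately.

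A reader might go further and infer that the study can say nothing about either disorder, that an alcohol effect will be published as an anxiety marker, or that controls sit at the floor of both scores. The documents support none of these. The scores vary within cases, no labelling rule is stated, and no control scores are reported.

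**Conclusion.** The point holds in a limited form. Confounding of the two conditions is complete for group status and needs no assumption. For the STAI and AUDIT scores it is strong but partial: over the assumed range, a sensor driven by alcohol alone shows a significant pooled association with STAI in about 11-85% of studies, where 5% would be nominal. The direction is secure; the size depends on separations that the article does not report, and larger ones would raise it. Within-case analysis with mutual adjustment brings the rate back to about 5%. Because this is a pilot and the combined phenotype remains estimable, the weight is moderate: it restricts what may be concluded and does not invalidate the study.

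**What to change.** Change the Background aim, the primary outcome section and Statistical Methods as follows.

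1. Describe the case-control contrast as the pattern of alcohol use disorder with anxiety symptoms, not of either disorder alone.
2. Beside the pooled results, report each sensor-score association and the model's prediction error within cases, with STAI and AUDIT entered together. Include a group term in any pooled model, because adjusting for AUDIT alone is not always enough.
3. Attribute a feature to anxiety or to alcohol only if its association persists within cases after this mutual adjustment.

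Add the anxiety-alcohol overlap to the limitations in the Discussion.

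The cost is wording and a few extra models on data already collected. The price is precision: single-disorder results rest on 29-30 cases, will look less favourable than pooled ones, and should be called exploratory.

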### Data Analysis

#### Overview

For each participant, we will collect data through a Fitbit and smartphone device, as well as written data through the form of questionnaires. The devices will offer insight into the physiological responses and changes within participants, which provides a more objective side of the data. For example, the heart rate monitor will report the intensity of one’s heartbeat and could suggest symptoms of anxiety. Additionally, the smartphone GPS will report a participant's movement and, therefore, insight into one’s daily energy or lethargy.

The written responses through questionnaires will give a subjective account of the participants’ anxiety or alcohol use disorder symptoms. An example of this is the STAI, which asks for a scalar rating on one’s feeling of lethargy. Using the data from the Fitbit and smartphone devices, plus the data from the questionnaires, we will determine any correlation.

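### The objective and primary outcome ask whether sensors can replace diagnosis, a question that a case-control pilot in people of already settled status cannot answer

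*Protocol article*

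**What the plan says.** **Aim.** Study Objectives begins with describing sensor patterns in two groups. It then gives the purpose: "to determine whether the use of sensor data is an efficient and accurate means of presenting objective diagnoses rather than the subjective diagnoses of the" present practice. Primary Outcome repeats this: the comparison is "to determine the feasibility and efficiency of using objective sensor data in place of the current subjective methods of diagnosing mental health disorders". The same section closes with "The primary outcome will be the efficiency of the developed algorithm’s ability to predict disorder symptoms". The route there has two steps: relate each sensor stream to symptom levels, then model the questionnaire scores from sensor data alone.

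**Yardstick.** Primary Outcome names the STAI and the DSM-5 as the gold standard. The Overview under Data Analysis says of the questionnaires: "The written responses through questionnaires will give a subjective account of the participants’ anxiety or alcohol use disorder symptoms".

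**Sample.** The Overview under Design states: "This study is a case-controlled, prospective study consisting of two groups". Study Objectives gives "60 participants split into two subgroups of 30 participants each". Study Population and Setting requires that cases "must have an alcohol use disorder, based on the Diagnostic and Statistical Manual of Mental Disorders, 5th Edition (DSM-5"), and that their STAI score lies above the 33rd percentile. Controls are healthy people without symptoms of either condition (Design, Overview), and current medication or substance abuse rules them out (first visit). Cases come from the hospital's Addictions Unit, controls from fliers, brochures and social media. The groups are matched for age and sex.

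**Status of the study.** The Discussion calls it a feasibility pilot. The limitations it discusses are depressive comorbidity, Android-only phones, age and familiarity, and small sample size.

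**The concern.** Whether a method can stand in for diagnosis is a question about people whose status is not yet known. Here every participant's status is settled before any sensor data exist, and the two groups sit at opposite ends of the range. People in between, such as volunteers with some symptoms, patients under assessment, or people with only one of the two conditions, are in neither group. Yet these are the people among whom a diagnostic tool has to work.

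The yardstick raises a second difficulty. The model is trained to reproduce scores that the article itself calls subjective. Close agreement would show that sensors can approximate those scores. It could not show that sensors are better than them, or more objective.

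What is at stake is how the result is read. Under the objective as worded, a good correlation or good separation of the groups would count as evidence that sensors can take the place of clinical diagnosis.

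**Working it through.** **1. The plan's own figure.** The only figure to check is the sample: 30 + 30 = 60, so the case share is 30/60 = 50%, set by recruitment. The article gives no inputs from which 60 could be derived. Sensitivity, specificity, prevalence, correlations and group gaps below are therefore assumptions.

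**2. Question against sample.**

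| Needed to judge replacement of diagnosis | What is enrolled |
|---|---|
| People of undetermined status | None |
| Cases and non-cases from one source | Addictions clinic against volunteers |
| The full range of severity | Clinic cases and symptom-free controls |
| A reference other than the method to be replaced | STAI and DSM-5, which also selected the cases |

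Matching on age and sex does not change any of these rows.

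**3. Effect of the range of severity.** Assume a standard normal severity, a sensor signal correlated with it at ρ, and cases as the top 20%. A simulation of 2 million people gives these AUCs:

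| Controls | ρ = 0.4 | ρ = 0.6 | ρ = 0.8 |
|---|---|---|---|
| Healthiest third | 0.78 | 0.89 | 0.98 |
| All non-cases | 0.70 | 0.80 | 0.90 |
| Near-miss non-cases (50th to 80th percentile) | 0.62 | 0.70 | 0.80 |

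The sensor is the same in every row; only the controls differ. Sensitivity and specificity at a given cut-off are affected for the same reason.

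**4. Pooled correlation.** Take equal groups with within-group SD 1, within-group correlation r_w, and mean gaps g (score) and h (sensor). Then

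r_pooled = (r_w + gh/4) / √[(1 + g²/4)(1 + h²/4)].

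With r_w = 0, g = 2 and h = 1: 0.5 / √(2 × 1.25) = 0.5 / 1.581 = 0.32. Smaller gaps, still with r_w = 0, give:

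- g = 1, h = 0.5: 0.11
- g = 1, h = 1: 0.20
- g = 1.5, h = 1: 0.27

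So a pooled correlation can come from the group difference alone, while sensors say nothing about symptom level inside either group.

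**5. What the 50% share does.** Sensitivity, specificity and AUC do not depend algebraically on the case share p. Two other quantities do.

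- Overall accuracy = se·p + sp·(1 − p). With se = 0.90 and sp = 0.70 it is 0.80 at p = 0.50 and 0.72 at p = 0.10. It stays constant only if se = sp.
- PPV = se·p / [se·p + (1 − sp)(1 − p)]. With se = sp = 0.85:

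| p | 0.50 | 0.30 | 0.20 | 0.10 | 0.05 |
|---|---|---|---|---|---|
| PPV | 0.85 | 0.71 | 0.59 | 0.39 | 0.23 |

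For se = sp from 0.80 to 0.90, PPV at p = 0.10 runs from 0.31 to 0.50. The value 0.85 borrows the highest accuracy quoted in the Background (up to 85%, for social anxiety in 54 college students). Using it as both sensitivity and specificity is an assumption.

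**The case against.** The operative parts of the plan are modest. The objective opens with describing patterns in two groups, and the primary outcome is prediction of symptoms through estimated questionnaire scores. That is close to the restatement proposed below. The study is called a feasibility pilot, a larger one is foreseen, and the article draws no diagnostic conclusion. Comparing clear cases with healthy controls is a legitimate first step. The scores are graded and repeated weekly, so agreement within a group or within a person does not depend on the 30:30 mix. For anxiety, entry rests on a symptom threshold and not on a diagnosis. Statistical Methods already summarises each group separately as well as together.

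Most of this stands, and it is why the design itself is not challenged. It does not remove the mismatch: the replacement aim appears in two places, neither is qualified by the pilot label, and the limitations do not mention it. Naming the DSM-5 beside the STAI does not help either. All cases have the DSM-5 alcohol diagnosis on entry, so comparing sensors with it amounts to telling the two recruited groups apart.

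Two stronger readings are tempting. A reader might infer that the study sets out to prove that sensors diagnose, but the text says only that it will determine whether they do. A reader might also infer that the 30:30 split makes every accuracy figure meaningless. Step 5 shows that the split bears on predictive values and overall accuracy; the main fault is the extreme groups and their separate sources.

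**Conclusion.** The point holds as a mismatch between claim and design. The replacement question cannot be answered from this sample with this yardstick, whatever the data show. What the study can give is proof-of-concept separation of two pre-selected groups and agreement between sensor-estimated and self-reported scores.

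The size can only be illustrated. In the simulation, moving from the healthiest controls to near-miss non-cases lowers the AUC by 0.16 to 0.20 (0.78 to 0.62, 0.89 to 0.70, 0.98 to 0.80). A pooled correlation of 0.11 to 0.32 can appear with none within groups. These figures rest on normal distributions and assumed gaps; they show that the effects can be material, not what this study will find. That discrimination is inflated is likely, given the groups, but not established.

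A reader might take the PPVs of 0.39 and 0.23 as a forecast of the study's performance. The documents do not support that: the article plans no predictive value and states no prevalence. Nor do they support calling the study worthless or in need of redesign.

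**What to change.** - In Study Objectives, delete the phrase that sets objective diagnoses against current subjective ones. In Primary Outcome, delete the phrase about using sensors in place of current diagnostic methods.
- Restate both as agreement between sensor-estimated and self-reported symptom scores in participants of known status.
- Report agreement within each group, separately from any pooled result.
- If case/control discrimination is reported, label it proof-of-concept separation of these two groups and give no predictive values. Sensitivity, specificity and AUC need the same label, since the choice of groups affects them too.
- Add to the limitations that diagnostic use needs a study in consecutive patients of undetermined status.

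No new data are needed. Collection ended in December 2019 and the article describes processing as still under way, so analysis and reporting could follow the narrower aim. The cost is some wording, one split of the analysis, and a more modest headline claim.
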